EKBB Ethikkommission beider Basel

FS Faecal sludge

FECT Formalin-ether concentration technique

HBT Health based targets

IWMI International Water Management Institute

KCCA Kampala Capital City Authority

MOH Ministry of public health in Kampala

MSW Municipal solid waste

NWSC National water and sewerage corporation

ODK Open data kit

PFA Pathogen flow analysis

QMRA Quantitative microbial risk assessment

RRR Recourse recovery and reuse

SANDEC Department of water and sanitation in developing countries

SDC Swiss agency for development and cooperation

SOPH School of Public Health in Kampala

SSP Sanitation Safety Plan

Swiss TPH Swiss Tropical and Public Health Institute

UNCST Uganda National Council of Science and Technology

WHO World Health Organization

WW Wastewater

Operational definitions

**Agro-industrial waste (AIW):** It includes a variety of waste products which arise at farm level. It can be plant material as well as animal excreta and remains.

**Business Model** **(BM)**: In this context we define it as a model that contributes to cost recovery or profit from reuse, ideally supporting in this way the sanitation service (e.g. wastewater treatment plant, faecal sludge management).

**Critical control points (CCP):** Is a point, step or procedure along a chain at which controls can be applied and hazards can be managed (prevented, eliminated or reduced) to reach tolerable risk levels.

**Cross-sectional study:** Is a descriptive study design to assess frequency and distribution of risk factors and/or disease outcomes. At one point in time a cross-section of the population at risk is sampled and examined.

**Dried Sludge**: Is found on drying beds where wastewater sludge from wastewater treatment plants is exposed to sun.

**Faecal sludge (FS):** Is raw (or partially digested) slurry or solid that results from the storage of black water or excreta. The composition of faecal sludge varies significantly depending on the location, water content and storage conditions. In general, faecal sludge can be distinguished between high strength (from latrines, non sewered public toilets) and low strength (from septic tanks).

**Hazard:** A biological, chemical, physical or radiological agent that has the potential to cause harm

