**Health based target:** A defined level of health protection for a given exposure. This can be based on a measure of disease (e.g. 10^-6^ DALY per person per year, WHO standard for wastewater, excreta and grey water reuse), or the absence of a specific disease related to that exposure

**Log reduction:** Organism removal efficiencies: 1 log unit = 90%, 2 log units = 99%; 3 log units = 99.9% and so on.

**Municipal solid waste (MSW):** Definition by OECD (2010): “Municipal waste is collected and treated by, or for municipalities. It covers waste from households, including bulky waste, similar waste from commerce and trade, office buildings, institutions and small businesses, yard and garden, street sweepings, contents of litter containers, and market cleansing. Waste from municipal sewage networks and treatment, as well as municipal construction and demolition is excluded”.

**Pathogen flow analysis (PFA):** Is a mathematical model to analysis pathogen along critical control points, from source to human exposure. Removal (e.g. log reduction due to treatment), inactivation as well as re-growth of pathogen can be simulated over time.

**Quantitative microbial risk assessment (QMRA):** Is an approach that can estimate risks for a variety of different exposures and/or pathogens that would be difficult to measure through epidemiological studies. It comprises following four steps: (i) hazard identification; (ii) dose response assessment; (iii) exposure assessment; and (iv) risk characterization.

**Resource recovery and reuse (RRR):** Is a project which aims to promote the safe recovery and reuse of water, nutrients and organic matter from liquid and solid waste streams with a focus on the assessment of perspectives, opportunities and challenges of business models (BM) and sanitation safety planning.

**Sanitation Safety Plan (SSP):** Is practical step-wise oriented guidance to facilitate the development of locally site specific assessment and management plans to reduce health impact from wastewater, excreta and greywater, while at the same time maximize the benefits of their use in productive agriculture and aquaculture.

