In Kampala, as under chapter 1.1 briefly described, within the Nakivubo area such recovery and reuse of partially treated WW and FS takes place. For example, the dried wastewater sludge is reused as soil adamant and the nutrients are recovered in flower industries in agriculture. The treated effluent is informally reused for unrestricted irrigation downstream of the plant within the Nakivubo swamp, where farmers grow root (e.g. potatoes, cocoyam) and leaf crops (e.g. salad). Although, this recovered waste products are beneficial for agriculture, such practices might pose risks for human and animal health (Cissé 1997; Keiser and Utzinger 2005; WHO 2006a; Do et al. 2007). Yet, the potential risks have to be fully understood and policies and regulations, which are mainly relying on the ‘WHO Guidelines for the Safe Use of Wastewater, Excreta’ (WHO 2006a-d) have to be adjusted to the local context of Kampala. Therefore, it is important to undertake further assessments along the WW and FS chains and analyse the health risks related to this exposures in more detail. Hence, there is a pressing need to promote adequate risk mitigation measures for exposed groups (workers and farmers) and to give specific recommendations to adjust guidelines and regulation in the sanitation sector for the city of Kampala (WHO 2006a-d).

- 1. Justification of proposed research

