Deduced to the specific objectives we assume that increased exposure to wastewater and faecal sludge results in higher infection rates of parasitic diseases and other water-related diseases outcomes. Therefore we intent to test following two hypotheses:

1. The difference in odds ratio is 2.5 or higher between highly exposed groups (people working along the wastewater and faecal sludge chain) and the people without an exposure to the two waste chains (control groups).
2. The helminth infection intensity decreases with the distance to wastewater treatment plant in Bugolobi and the Nakivubo swamp.
3. Methodology
   1. Study site

Kampala is the capital and largest city of Uganda with a resident population of 1,597,500 people who live on an area of 197 km² (UBOS, 2010). This population nearly doubles during the day due to people who live in the neighbouring areas and travel to Kampala on a daily basis. The city has a [tropical climate](http://en.wikipedia.org/wiki/Tropical_wet_and_dry_climate) but because of the high altitude (1,190 m above sea level) the average temperature (16°C -28°C) is relatively cool compared to other lower altitude East African settings. The main rain season is between March and May and the short rain season is between November and December. Rainfall ranges between 500 mm and 2500 mm and the relative humidity is between 70% and 100% (Figure 1) (IWMI, 2012a).

The specific study site will be around the WW and FS treatment plant BSTDW and the Nakivubo swamp. It is located in an urban context of Kampala and surrounded by high density neighbourhoods in between Nakawa and Makindye divisions. The plant is operated by the NWSC and was constructed prior to the 1940s by the British and subsequently extended during the periods of 1956/1958. The WW entering the plant is treated via primary (grit and detritus removal and primary sedimentation), and secondary processes (effluent: trickling filter system secondary sedimentation; and WW sludge: anaerobic digestion ponds and drying beds). The secondary treated effluent is then led through a natural wetland (Nakivubo swamp) where it is tertiary treated before it is discharged into Lake Victoria (Figure 2). There are plans that the BSTDW is put out of service within the next 4-6 years, and replaced by a new plant. At the moment, NWSC and KCCA are conducting studies to determine the most appropriate treatment processes for this context.

[figure not shown]

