| Faecal coliform (CFU/100 ml) | **10’000** | 52’000’000 | 68’000 | 134’000 | 142’000 |
| pH | **6.0-8.0** | 8 | 8 | 8 | 8 |
| Ortho Phosphate (mg/L) | **5** | 13 | 7 | 9 | 10 |
| Total Phosphate (mg/L) | **10** | 13 | 7 | 10 | 10 |
| Total Alkalinity (mg/l as CaCO_3_) | **700** | 480 | 460 | 400 | 420 |
| Total Suspended Solids (mg/l) | **100** | 788 | 74 | 395 | 450 |

We will sample over a period of two month 1 l of WW twice a week and three times per day (once between 9-10 am, 2-3 pm and 5-6 pm)) to take into account the daily variance. The WW and FS samples will be taken form five sources, namely: (i) raw sewage; (ii) final effluent; (iii) raw effluent of the FS; (iv) water of the Nakivubo channel; and (v) water within the Nakivubo swamp (Figure 3). In addition we also want to analyse the dried sludge in the drying beds. Therefore, we will take samples from five points in five drying beds twice a week over a period of 2 months (Figure 4).

All the samples will be collected and prepared (sedimentation and centrifugation) by lab personal of the BSTDW and handed over to the laboratory of the vector control division of the MOH for further preparation and analysis of the pathogens as described below.

[figure not shown]

**Figure 6.** Simplified process flow diagram of the study site around National Water and Sewerage Corporation in Bugolobi. Blue colour indicates the sample points for the testing for helminth eggs and intestinal protozoa cysts. (i) raw sewage; (ii) final effluent; (iii) raw effluent of the faecal sludge; and (vi) Nakivubo channel and (v) in the Nakivubo swamp and (vi) dried sludge.

- - - 1. Laboratory analysis of wastewater and faecal sludge

To analyse the various WW samples and the FS effluent we will use the modified Bailenger method (Ayres et al. 1996) which is recommended by WHO to analyse WW. With this method we can successfully recover a wide range of helminth eggs including *A.lumbricoides, T.trichiura*, *Capillaria* spp., *Enterobius vermicularis*, *Toxocara* spp., *Taenia* spp., *Hymenolepis* spp., and hookworm eggs. The procedure involves sedimentation of the sample for about 1 hour, centrifugation of the sediment and extraction with ether. Later it is mixed with zinc sulphate solution and applied on a McMaster slide for examination of helminth eggs under a microscope.

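### Drying-bed sampling as written records no bed age and no incoming sludge, so the drying-step reduction cannot be reliably calculated and the QMRA dose may mix fresh with reuse-ready sludge

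*Combined protocol and SAP*

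**What the plan says.** Section 4.2.2.1 (Data collection, objective 2) names five liquid sources: "i) raw sewage; (ii) final effluent; (iii) raw effluent of the FS; (iv) water of the Nakivubo channel; and (v) water within the Nakivubo swamp". It then adds the beds: "In addition we also want to analyse the dried sludge in the drying beds", and "we will take samples from five points in five drying beds twice a week over a period of 2 months". The caption of Figure 6 lists the same six points.

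Section 4.1 (Study site) describes the solids line as "WW sludge: anaerobic digestion ponds and drying beds". The beds are therefore fed with wastewater sludge, listed after the digestion ponds, and no sampling point is the pond outlet or the bed inlet. The operational definition of dried sludge goes by location: it "Is found on drying beds where wastewater sludge from wastewater treatment plants is exposed to sun". It sets no dryness or readiness threshold.

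The operational definition of pathogen flow analysis (PFA) states: "Removal (e.g. log reduction due to treatment), inactivation as well as re-growth of pathogen can be simulated over time". Section 2.4 counts drying among the processes that lower pathogen concentration and says a barrier is judged by its log reduction and by the variation in that reduction. Section 1.2 says that "the dried wastewater sludge is reused as soil adamant". Section 4.2.3 passes PFA concentrations to the QMRA.

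Section 4.2.2.2 analyses wastewater and faecal sludge effluent by the modified Bailenger method. Dried sludge is analysed by the same Kato-Katz and formalin-ether techniques used for stool. Section 4.2.1.5 gives the Kato-Katz template as 41.7 mg.

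**The concern.** A drying bed is a batch process. A sample from it can be interpreted only if one knows how long the sludge has been there. Under this plan a sample from a bed filled yesterday and one from a bed about to be emptied carry the same label, and a bed could be emptied and refilled between visits without the data showing it. Bed age has to be captured at sampling and may not be recoverable afterwards.

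Two uses of the data are at stake. One is the barrier effect of drying, which is the kind of quantity the PFA is described as providing. The other is the dose for people who handle reused sludge or eat crops grown with it, for whom the relevant concentration is that at removal. Consumers of products grown with dried sludge are named in section 3 among the people potentially affected.

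**Working it through.** **1. The planned sampling volume.** Points per visit: 5 points × 5 beds = 25. Visits: 2 per week × 8 weeks (2 months taken as 8 weeks) = 16. Total: 25 × 16 = 400. The sludge Kato-Katz line in section 8 (Estimated budget) gives 25 × 16 = 400, so the figure is reproduced at one slide per sample. The plan states no power, target log reduction or precision for this component.

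**2. What is needed against what is planned.**

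| Needed for a drying-step reduction | In the plan |
|---|---|
| Concentration of sludge entering the bed | Not a sampling point |
| Concentration at removal | Beds sampled, but ready beds not identified |
| Time between the two | Visit dates only; no fill or emptying date |
| Same bed followed | Not stated |
| Comparable unit at both ends | Kato-Katz by fixed template, no moisture measurement named |

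Raw sewage and faecal sludge effluent are poor substitutes for the missing inlet: they are different materials, and their eggs are counted by a different method.

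**3. What repeat visits could still show.** If the same beds are followed, a within-bed slope could be estimated, but the total reduction is slope × drying time. With an assumed slope of 0.02 to 0.05 log10 per day:
- 14 days: 0.02 × 14 = 0.28 to 0.05 × 14 = 0.70 log10
- 56 days: 0.02 × 56 = 1.12 to 0.05 × 56 = 2.80 log10

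The same slope is thus compatible with a fourfold range in total log reduction when drying time is unknown. A 56-day window holds 56/14 = 4 cycles of 14 days but only 56/56 = 1 cycle of 56 days, and that one is complete only if the bed is filled as sampling starts.

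**4. Size of the dose error if all stages were averaged.** Assumptions, none from the documents: concentration per dry mass falls log-linearly by L logs over the cycle, and sampled bed ages are spread evenly over it.

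Mean over the cycle = C0 × (1 − 10^−L)/(L ln 10). Concentration at removal = C0 × 10^−L. Ratio = (10^L − 1)/(L ln 10).

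| L (log10) | Calculation | Ratio |
|---|---|---|
| 0 | limit | 1 |
| 0.25 | 0.778/0.576 | 1.4 |
| 0.5 | 2.162/1.151 | 1.9 |
| 1 | 9/2.303 | 3.9 |
| 2 | 99/4.605 | 21.5 |

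Without bed age the study could not tell which row applies.

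**5. Unit of the counts.** A fixed template measures eggs per mass of sludge as it lies on the bed. As water is lost, eggs per wet mass can rise even while eggs per dry mass fall. Counts plotted against days since filling would therefore combine water loss and egg decline.

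**The case against.** The case against has several fair parts.

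- **The plan is silent; it does not decline to record dates.** The sampling form is not among the documents, plant laboratory staff collect the samples, and section 4.2.2.1 leaves room for other obtainable parameters. Dates may well be available. This stands as a reason to expect the fix to be easy. It does not close the gap, because that wording concerns trend data on contamination and nothing asks for bed records.
- **A reader might infer that the QMRA dose averages fresh and reuse-ready sludge.** The documents do not support that. They state no pooling rule, name dried sludge as the target, and plan Monte Carlo simulation with an evaluation of uncertainty. What is supportable is that nothing keeps the stages apart, so the dose may mix them.
- **A reader might infer that the reduction cannot be calculated at all, or that the sampling yields no input or output.** That is too strong. If the same beds are followed, the 400 samples may include early and late material and show a trend. What is missing is chiefly the labelling, plus a unit that is not altered by drying.
- **No drying-step log reduction is promised.** Section 4.2.2.3 promises hazards at control points and a correlation with disease outcomes, and neither hypothesis uses bed data. This limits the weight of the point, but sections 2.4 and 2.5 and the PFA definition still make reduction at barriers part of the method's purpose.
- **Sludge at earlier stages may matter for workers operating the plant (W1).** This stands. Discarding those samples would be a mistake, and the fix keeps them.

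**Conclusion.** The point holds in a limited form. As written, the data collection captures no bed age, does not fix which beds are followed, and has no sample of the incoming sludge. The drying-step reduction therefore cannot be reliably calculated, and fresh sludge cannot be told from sludge ready for reuse. The possible overstatement of the reuse dose is 1 to about 21 times for a fall of 0 to 2 logs. This is conditional on averaging across all stages, evenly spread bed ages and log-linear decline per dry mass; the documents give no decline rate or cycle length. The effect is confined to one control point and one QMRA input. The cross-sectional survey and its two hypotheses are untouched. It deserves correction before sampling starts because the remedy is simple then and may be impossible later.

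**What to change.** **Record.** At each visit note, with the plant operator's help, a bed identifier, the date filled, the date emptied or refilled, days since filling, and whether the bed is ready for removal.

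**Dose.** Use only ready-for-removal samples for the reuse dose (users and consumers). Keep samples from all stages for W1 exposure.

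**Drying step.** Describe counts by days since filling, with bed as a cluster. Take the first and last samples of a cycle as approximate input and output only where a full fill-to-removal cycle has been observed. Do not call the change a log reduction unless counts are expressed per dry mass, because wet-mass Kato-Katz counts also move with water loss.

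**Cost.** A few fields on the sample form and a regrouping of the planned 400 samples; no extra samples. Reporting per dry mass would need a moisture measurement, which the plan does not name. The downsides are that fewer samples inform the reuse dose and that some beds may not complete a cycle within 2 months. In that case the report should say that no reduction could be estimated for them.

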**Methods**: The study is composed of three parts: Part 1: a cross-sectional study with 1000 participants to assess the existing exposure risks due to wastewater and faecal sludge in directly exposed groups (includes 150 workers and 275 farmers), and partially and non-exposed groups as a control group (includes 575 communities members) with a specific focus on parasitic infections, skin diseases, eye diseases, and diarrhoeal episodes. The survey comprises of two components: (i) a questionnaire study to obtain health risk and health outcomes related to the exposure to wastewater and faecal sludge; and (ii) the collection of stool samples to determine the prevalence and the intensity of helminth (with the Kato-Katz method) and of intestinal protozoa infections (with the formalin-ether concentration technique); Part 2: a pathogen flow analysis to observe the variance of pathogen contamination at critical control points over time, we will assess existing operational monitoring data and analyse over a period of two month wastewater and faecal sludge for helminth eggs (modified Bailenger method) and intestinal protozoa cysts (formalin-ether concentration technique); and Part 3: a quantitative microbial assessment interlinked to the pathogen flow analysis to estimate diarrhoeal and parasitic infection risk and validate the results with the findings obtained under objective 1. Finally, with a subset of the stool and wastewater samples we will perform PCR for species detection and/or meta-genomic analysis in order to provide quantitative insights into microbial population based on sequence data.

**Expected results**: We will generate evidence and fill knowledge gaps on diseases outcomes related to the exposure to wastewater and faecal sludge. Based on these results we will be able to make evidence-based recommendations of the most appropriate combination of health protection measures to achieve context specific health base targets along the wastewater and faecal sludge chains and contribute to the sanitation safety plans processes. Hence, this study can help to promote the safe recovery and reuse of water and nutrients along these two waste chains and will benefit the planning of new wastewater and faecal sludge treatment plants and/or solutions in Kampala city.

Acronyms and Abbreviations

AIW Agro-industrial waste

BSTDW Bugolobi sewerage, treatment and disposal works

CCP Critical control points

Eawag Swiss Federal Institute of Aquatic Science and Technology

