For each stool sample duplicate Kato-Katz thick smears will be prepared, using standard 41.7 mg template. The slides will be labelled with the participants unique ID plus ether ‘A’ (first Kato-Katz) or ‘B’ (second Kato-Katz) and allowed to dry for at least 30 minutes. Slides will be examined quantitatively under a light microscope by 1 laboratory technicians. For each slide the number of helminths (*A.lumbricoides*, hookworm, *T.trichiura* and *S.mansoni* and other helminth) will be counted and recorded separately.

Additionally, for each stool sample we will perform a FECT to detect protozoa infections. In short, approximately 1 g of the stool will be placed in a tube containing 10 ml of formalin and labelled again with the unique ID number of the participant plus a C. The sample will be mixed, centrifuged and the supernatant removed. 7 ml saline solution will be added, mixed and centrifuged. The sediment is the examined on presence of helminth eggs and intestinal protozoa cysts under a light microscope.

For quality control 10% of all the Kato-Katz slides will be re-examined by an external person (e.g. PhD student), the results of the *A.lumbricoides, T.trichiura* and *S.mansoni* egg counts compared and any discrepancies removed by re-examining the discordant slides.

A subset of the stool samples (100-150 samples) will be frozen (-20°C) and transferred to Swiss TPH in Switzerland for pending polymerase chain reaction (PCR) for species detection and/or meta-genomic analysis in order to provide quantitative insights into microbial population based on sequence data.

- - - 1. Study variables for the cross sectional survey
         1. *Dependent variables*

As dependent variables we will measure the prevalence of all detected parasitic infection (helminth and intestinal protozoa) and the intensity of helminth infections in the stool samples. For the questionnaire study we will ask the participants questions about symptoms and signs of certain disease outcomes to estimate the prevalence of fever and skin, eye, reparatory diseases and diarrhoea episodes within a two week recall period.

- - - - 1. *Independent variables*

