A second multilevel regression analysis aims to test the hypothesis 2, which expects a potential association between helminth egg counts and the distance to the water treatment plant and the Nakivubo swamp. We will define x as equal the distance from water treatment plant and Nakivubo swamp (1 = maximal distance and 0 = living or working directly at the plant or Nakivubo swamp). A true difference in average logarithmized egg counts of 0.8 individual standard deviations between subjects with x = 0 and subjects with x =1 would guarantee 95% power of finding a statistically significant association and would leave room for covariate adjustment. To verify the hypothesis we would assume that a difference of 0.8 standard deviations corresponds to a situation where the median egg count of the highest exposure group (with x=0) is at the 80^th^ percentile of the lowest exposure group (with x = 1).

- - - 1. Expected outcomes

With the cross-sectional study approach will create scientific evidence on the exposure risk to the WW and FS and are able to map the health risk along two waste chains in the Nakivubo area. Hence, we will test if the assumption made in hypothesis 1 and 2 are true to verify or falsify the hypothesis.

- - 1. Study design for objective 2

**Approach:** We will establish a PFA along the WW and FS chain around the BTWP and the Nakavibu swamp in Kampala. We will follow the pathogen concentration of faecal coliform, helminth egg and intestinal protozoa cysts over time.

- - - 1. Data collection

To establish a PFA we intent to use as a backbone of the model secondary data (e.g. obtained during the routine quality data collected by the BTWP (Table 3)) and will conduct a trend analysis for the pathogens and contaminations of interest (faecal coliforms, pH and other relevant parameters which can be obtained) over time. Additionally, we will analyse the WW and FS over a period of 2 months for helminth eggs and intestinal protozoa cysts.

**Table 7** Quality testing of WW at various sources within and around the Bugolobi sewerage, treatment and disposal works

| **Reported Data: 09.01.2013** | **Standard** | **Raw sewage** | **Final effluent** | **Nakivubo channel** | **Nakivubo wetland** |
| --- | --- | --- | --- | --- | --- |
| Ammonia –N (mg/l) | **10** | 43 | 12 | 8 | 10 |
| BOD_5_ (mg/l) | **50** | 465 | 122 | 134 | 288 |
| COD (mg/l) | **100** | 889 | 239 | 258 | 266 |
| Conductivity (nS/cm) | **1’500** | 1’049 | 1’097 | 998 | 1’025 |

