For the analysis of the dried sludge we will use the same Kato-Katz technique and FECT technique previously described for the examination of the stool samples for helminth eggs or for intestinal protozoa respectively.

A random sub sample (100-150 samples) of the collected wastewater and faecal sludge samples will be transferred to Switzerland for pending polymerase chain reaction (PCR) for species detection and/or meta-genomic analysis in order to provide quantitative insights into microbial population based on sequence data. The pathogen sequence data found in the wastewater and faecal sludge are then further compared with the pathogen sequence data found in the stool samples of the participants of the cross-sectional survey.

- - - 1. Expected outcomes

The outcomes of the PFA will indicate specific hazards at critical control points along the WW and FS chains over time. This helps us to determine a correlation between the pathogen concentrations and the disease outcomes obtained under objective 1 in exposure groups along the WW and FS chain.

- - 1. Study design for objective 3

Approach: We will use the data on faecal coliform, helminth egg (e.g. *A.lumbricoides* egg) and intestinal protozoa cyst (e.g. *Cryptosporidium parvum* cyst) concentrations determined for specific critical control points in the PFA and interlink them with a QMRA.

- - - 1. Model concept

Haas et al. (1999) described QMRA as an iterative approach in the following four steps to estimate health risks: (i) hazard identification (identify relevant pathogens, in our case faecal coliforms, *A.lumbricoides*, *C.parvum*); (ii) dose-response assessment (Relationship between doses and negative health effect on exposed population, data for the selected pathogen can be accessed in the literature); (iii) exposure assessment (estimate frequency, amount and duration of exposure for relevant transmission routes, will be assessed in the interviews with exposed groups); (iv) risk characterization (estimate public health risk, and evaluate uncertainty and sensitivity).

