We will develop different exposure scenarios (e.g. involuntary soil or wastewater ingestion) (WHO 2006b; Mara 2007; Mara 2010) to estimate the theoretical *A.lumbricoides* egg and *Cryptosporidium parvum* infection risk and diarrhoeal risks to for different exposed groups. Therefore we will run series risk simulation using a QMRA-Monte Carlo computer program (Karavarsamis and Hamilton 2010) for calculating annual risk (program can be downloaded from www.personal.leeds.ac.uk). Finally, these simulated exposure risks will then be compared and validated with the parasitic infection data obtain under objective 1.

- - - 1. Expected outcomes

With these results we will be able to make simulation-based recommendations of the most appropriate combination of health protection measures to achieve context specific HBT for different types of reuse practises, for example, for unrestricted irrigation (crop consumers e.g. for lettuce and onion farming) and restricted irrigation (farmers and workers e.g. working in highly mechanized or labour intensive agriculture). These results can also benefit the sanitation sector in general, and the planning of new WW and FS treatment plants in Kampala city.

1. Ethical considerations
   1. Ethical Committee Review

The study proposal will be reviewed by the institutional research commission of the Swiss TPH, the ‘Ethikkommission beider Basel’ (EKBB) and the Makerere University School of Public Health: Higher Degrees Research and Ethics Committee and the Uganda National Council of Science and Technology (UNCST) in Kampala, Uganda.

- 1. Confidentiality

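### The source of the C. parvum dose for the QMRA is undefined: section 4.2.2.2 gives the liquid samples no protozoan method, and FECT is read for presence only

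*Combined protocol and SAP*

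**What the plan says.** **What is needed.** The Approach paragraph of 4.2.2 commits to concentrations: "We will follow the pathogen concentration of faecal coliform, helminth egg and intestinal protozoa cysts over time". The Approach paragraph of 4.2.3 then takes the "concentrations determined for specific critical control points in the PFA and interlink them with a QMRA", with C. parvum as the protozoan example. Section 4.2.3.1 names C. parvum among the QMRA pathogens, simulates its "infection risk and diarrhoeal risks to for different exposed groups", and compares the simulated risks with the infection data from objective 1.

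**What the laboratory section assigns.** For liquids, 4.2.2.2 says: "To analyse the various WW samples and the FS effluent we will use the modified Bailenger method". The organisms it lists as recoverable are all helminths, and the extract is "applied on a McMaster slide for examination of helminth eggs under a microscope". FECT appears in 4.2.2.2 only for dried sludge, by reference back to the stool method. That method, in 4.2.1.5, ends: "The sediment is the examined on presence of helminth eggs and intestinal protozoa cysts under a light microscope".

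**What other parts say.** The Abstract plans to analyse "wastewater and faecal sludge for helminth eggs (modified Bailenger method) and intestinal protozoa cysts (formalin-ether concentration technique"). Section 4.2.2.1 also plans cyst analysis of wastewater and faecal sludge, and the Figure 6 caption marks all six sampling points for egg and cyst testing.

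**PCR subset.** Section 4.2.2.2 sends a random 100-150 wastewater and faecal sludge samples for PCR and/or metagenomics. It describes the result as quantitative, but the stated use is comparison with sequences from stool.

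**The concern.** In a QMRA the dose is concentration multiplied by amount ingested. Section 4.2.3.1 takes the dose-response relation from the literature and the exposure from interviews and scenarios. The concentration is therefore the one microbial input measured at the site. If the C. parvum concentration has no defined source, someone will have to supply a value at analysis. The resulting risk could then be read as a Kampala measurement when it is an assumption.

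The plan intends to use these simulations to recommend health protection measures and to inform the planning of treatment plants. It also intends to check them against objective 1. If the two disagreed for C. parvum, the disagreement could not be attributed to the model, to the assumed dose or to the assay.

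**Working it through.** No stated sample size or power figure is involved. The check is whether any planned step ends in cysts per litre or per gram.

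**Step 1: trace each sample type.**
- *Liquids (raw sewage, final effluent, faecal sludge effluent, channel, swamp).* 4.2.2.2: Bailenger, read for helminth eggs, with no protozoan reading. The Abstract, 4.2.2.1 and Figure 6 expect one. The documents contradict each other here.
- *Dried sludge.* FECT, as for stool. The stool text gives a starting amount of about 1 g in 10 ml formalin. It gives no fraction of sediment read, no count and no detection limit.
- *Liquids if the Abstract prevails.* FECT again, so the same presence reading. The volume collected is 1 litre, but the volume represented by the portion read is not given.
- *Cryptosporidium.* No assay is named for environmental or stool samples.

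No route ends in a concentration.

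**Step 2: number of samples.** Assume two months is 8 weeks, which agrees with the multiplier of 16 in the budget's sampling lines.
- Sampling days: 2 × 8 = 16.
- Per liquid source: 16 × 3 = 48. Five sources: 5 × 48 = 240.
- Dried sludge: 5 points × 5 beds × 16 = 400. Total: 640.
- PCR subset: 100/640 = 16% to 150/640 = 23%. Against the budget's count of 18 × 16 = 288 wastewater and sludge samples, it is 35% to 52%.

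**Step 3: what presence data alone could give.** Assume Poisson-distributed cysts, a constant concentration, independent samples and complete recovery. With k of n portions positive, the mean per portion examined is λ = −ln(1 − k/n). Two-sided 95% limits come from the Clopper-Pearson limits for k/n. The values of k are illustrative, and n = 48:

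| k positive | λ per portion examined | 95% limits |
|---|---|---|
| 0 | 0 | upper limit 0.08 |
| 12 | 0.29 | 0.15 to 0.50 |
| 24 | 0.69 | 0.43 to 1.04 |
| 43 | 2.26 | 1.49 to 3.36 |
| 48 | not estimable | lower limit 2.6 |

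For k = 48 the lower limit of the proportion is 0.025^(1/48) = 0.926, and −ln(1 − 0.926) = 2.6. For k = 0 the upper limit is 1 − 0.926 = 0.074, and −ln(1 − 0.074) = 0.08.

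**Step 4: from portion to litre.** Concentration = λ / (V × r), where V is the volume of original sample represented in the portion read and r is the recovery. Neither is stated. As an illustration only, take r = 1 and V anywhere from 0.01 to 1 litre (assumption). The 24-of-48 result then means anything from 0.69/1 = 0.69 to 0.69/0.01 = 69 cysts per litre. The 100-fold spread is simply the assumed range of V, and it shows that the missing volume sets the answer.

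**Step 5: change over time.** The λ above pools two months into one average per source. A single yes/no reading does not give a concentration for one sampling time, which is what objective 2 sets out to follow.

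**The case against.** The strongest reply is that cyst testing of the liquids is planned. The Abstract, 4.2.2.1 and Figure 6 all say so, and only 4.2.2.2 leaves it out. This stands: a reader of 4.2.2.2 alone might infer that no protozoan test of wastewater was intended, and the rest of the document does not support that. It is a contradiction to reconcile. Resolving it in favour of the Abstract still leaves a presence reading.

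Second, a reader might infer that no protozoan dose can be calculated at all. That is too strong. Presence or absence in known amounts supports a bounded estimate, as step 3 shows, and the PCR subset is described as quantitative. Neither route is specified or linked to the QMRA, however, and the conversion in step 4 lacks its inputs.

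Third, the FECT description says that it is abridged, so a fuller procedure may exist. That is possible, but the counting unit and the amount read belong in the plan when a model depends on them.

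Fourth, the budget has 1,000 FECT slides for 1,000 stool samples (50 + 100 + 275 + 225 + 350), and a reader might conclude that no environmental FECT is intended. This is weak evidence, because Bailenger analysis has no line either.

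Finally, a reader might infer that this microscopy would miss Cryptosporidium, so that the QMRA would seem to over-predict. The documents are silent on staining and on sensitivity, and no such claim is made here.

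**Conclusion.** The concern holds for the protozoan arm of objective 3, and for the cyst concentrations promised under objective 2. Followed as written, the laboratory section yields no cysts per litre or gram, the documents disagree on whether liquids get a protozoan test, and the source of the C. parvum dose is undefined. The C. parvum infection risk, and any diarrhoeal risk built on it, would rest on an undeclared assumption.

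The size of any resulting error cannot be derived from the documents. The figures in steps 3 and 4 illustrate it under the assumptions stated there. Hypotheses 1 and 2 are untouched. The faecal coliform arm (counts in Table 7) and the helminth arm (an assigned method) are unaffected. This should be corrected before sampling starts, because the amount read cannot be reconstructed afterwards.

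**What to change.** 1. **Section 4.2.2.2:** assign the five liquid sources a protozoan method, and bring the Abstract, 4.2.2.1, Figure 6 and 4.2.2.2 into agreement.
2. **Section 4.2.2.2:** for environmental samples, replace the presence reading with a cyst count in a recorded aliquot. Record the original volume or mass, the final volume and the amount read. Report cysts per litre or per gram with a detection limit.
3. **Section 4.2.3.1:** state how non-detects enter the Monte Carlo input, for example as values bounded by the detection limit.
4. **Section 4.2.3:** keep C. parvum only if a named quantitative assay supplies its concentration (for example, a quantitative target on the PCR subset already planned) or another dose source is declared. Otherwise remove it from the QMRA and from the comparison with objective 1.

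The cost is wording in these sections, somewhat more microscopy time for counting, and possibly one added target on PCR that is already planned. The main downside is that the QMRA may lose its C. parvum arm.
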